### Physical activity

Physical activity change is measured using Actigraph GT3X and GT3X + accelerometers (Actigraph, Pensacola, Florida, USA) Accelerometers are worn during waking hours for seven consecutive days (excluding bathing and swimming) on the right hip, with movement assessed using sampling intervals (epochs) of 60 seconds. Accelerometers have been shown to be reliable and valid measures of physical activity participation in community samples, including overweight or obese adults [45]. During the measurement week, participants record wearing times using a diary. This aids with identifying non-wear periods; defined in this study as a consecutive string of 0 counts for 45 minutes (drop-time tolerance of three minutes). These criteria were developed following testing with a subset of data generated from study participants and is aligned with criteria used in other studies and best practice guidelines [46-48]. Participants with at least four valid days of data monitoring will be considered as having a valid dataset. A second measurement week is used if wear time criteria has not been met during the first measurement week. In this study, percentage wear-time is used for assessing a valid day. Specifically, a day is considered ‘valid’ if non-missing data are available for at least 70% of common wear-time hours (standardized for the hours each day where at least 70% of participants are found to be wearing the monitor). The benefits of this approach (compared with a more traditional approach including only days with >10 hours data recorded [49]) are that incomplete hours can be counted towards total wear-time. Furthermore, women with infants may keep different waking hours from the general population and may take the accelerometer off and on more frequently (for example, due to sleeping during the day). This approach was used in a recent accelerometry study conducted among pregnant and postnatal women [47].

At the end of the measurement week, the 7-Day PAR interview is administered to participants [50]. This method uses standardized prompts to encourage participants to recall the duration and intensity of activities, such as walking for transport, participation in structured exercise, home and work-based activities, and so on*.* Previous research has found that this is a reliable and valid method for measuring habitual physical activity [51]. The 7-Day PAR provides information regarding activity that is not assessed by the activity monitors (for example*,* swimming). Participants are also asked whether the activity levels during the previous week were “less than”, “more than” or “about the same” as the last three months and provide reasons for deviations from normal activity. This explanatory data will aid in interpretation of trial data.

### Secondary outcomes

#### Psychological well-being and fatigue

Psychological well-being is measured using the Adapted General Well-being Index (AGWI) [52]. The original General Well-being Index was developed in the United States and has been adapted for use in the UK. The AGWI consists of 22 items to assess positive well-being, self-control, anxiety and depression, vitality and general health concerns. Each statement is assessed using a five-point Likert response scale in relation to “the past two weeks” and a total well-being score is created by summing questions (negatively worded questions are reverse coded). The AGWI has been shown to have good reliability and validity with the Montgomery-Asberg Depression Rating Scale [53]. It has also been validated within a GP practice sample in the UK against several relevant criterion measures of subjective well-being, including global health status, reporting of ongoing psychological health problems (for example, depression), contact with health professionals, use of antidepressant medicine, tranquillizers or sleeping pills, common psychosocial worries or difficulties and having been unemployed in the last year [53]. Fatigue is measured using one question through a visual analogue scale (VAS). Visual analogue scales are a commonly used uni-dimensional method of assessing health status [54]. Participants place a mark on a 100 mm line to indicate their fatigue levels where no fatigue = 0 and worst possible fatigue = 100. The response category will be whether or not participants have been “affected by fatigue in the past two weeks”.

#### Cardiovascular fitness

Cardiovascular fitness is measured using the Chester Step Test [55]. The Chester Step Test is a sub-maximal fitness test that involves asking participants to step up and down on and off of a standardized step repeatedly in two-minute slots up to a maximum of ten minutes. Stepping rate is determined by a beep that increases after each slot. Participants wear a heart rate monitor (Polar Wearlink WIND chest transmitter, Polar Electro Inc., Lake Success, NY, USA with readings transmitted to a wrist-watch (Polar RS800, Polar Electro Inc., Lake Success, NY, USA) Heart rate is recorded at the end of each slot and the Rating of Perceived Exertion (RPE) scale [56] is used to indicate participants’ perception of activity intensity. The test continues until the participant reaches a heart rate (HR) that is 80% of their age-predicted maximum HR (220-participants age) or until they report an RPE of 14 or above (corresponding to perceiving the activity to be at least “hard”). Cardiovascular fitness (aerobic capacity) is predicted using a standardized equation using the number of slots completed and heart rate at termination of the test. The Chester Step Test has good validity as a predictor of cardiovascular fitness, measured against a maximal fitness test and it can be used with adults of all ages, including participants who are sedentary and overweight [55]. The test is conducted according to the Chester Step Test manual [57] and by using a step size of (8”/20 cm) as this is recommended for participants aged 40 and under undertaking little regular exercise. Prior to commencing the first test, participants take part in a two-minute familiarization period to avoid them experiencing a learning effect. Standardized encouragement was provided during the test.

#### Weight, BMI and body composition

Height is measured in centimeters (to the nearest cm) using a stadiometer (Leicester Portable Height Measure, Seca GmBH & Co Kg, Hamburg, Germany). Height readings are taken twice and averaged at the first baseline appointment. Weight and body composition (% fat mass) are measured using the Tanita portable bioelectrical impedance monitor (Tanita 300MA Tanita Europe B.V., Amsterdam, The Netherlands) according to the measurement protocol specified in the handbook (Tanita, technical notes). Weight is measured in kilograms (to the nearest 0.1 kg) and BMI computed as the participant’s weight in kilograms divided by their height in meters squared (kg/m^2^).

#### Psychological mediators

Psychological mediators are measured *via* a self-completion questionnaire that has been developed for this study from adapted measures used in previous studies [58-62]. The reliability of all questionnaire items will be tested in the study using Cronbach’s alpha for each proposed mediator, which are measured using 4 to 7-point Likert scales (for example, very unlikely – very likely, completely untrue - completely true *etc.*). Mediators measured in this study are specifically those targeted by the intervention methods (*for example,* outcome expectancies, self-efficacy, intentions to be active, action and coping planning and self-regulatory actions). Self-efficacy (*for example,* “How confident are you that you can be regularly physically active during the next three months…even if I’m tired”, and so on*.*) and outcomes expectancy measures (“If I were regularly physically active during the next three months…I would be healthier” and so on*.*) were sensitive to the most frequent barriers and enablers to activity cited by postnatal women; taken from a survey 667 postnatal women [63]. Intentions are operationalized using one item: “During the next three months do you intend to be regularly physically active?” [58]. Action planning is measured using four items following the stem: “I have made a detailed plan about being regularly physically active during the next three months…” (for example, how/when/where/how often). Coping planning, in contrast, asks participants to rate three items; for example, the extent to which they “have a detailed plan about what to do if things get in the way of them being regularly physically active during the next three months”. Planning measures have been validated in previous studies [61]. Six items are used to measure self-regulatory effort, adapted from the action control questionnaire used by Sniehotta *et al.*[62]. Example statements are: “During the last three months…I have been aware of how much physical activity I should be doing to meet my personal standards. I have made sure to monitor how much physical activity I’ve done and I have tried really hard to be physically active.”

#### Process measures

In line with CONSORT [29], trial process information will be reported to include information on the number of postnatal women who expressed an interest in joining the study, the numbers who were eligible and drop-outs at each trial stage. Demographic details collected from trial participants will be compared with decliners and ineligible women to assess representativeness in terms of their age, infant’s age, physical activity stage of change and deprivation status as measured by the Scottish Index of Multiple Deprivation (SIMD) [64]. To identify whether the intervention is delivered as intended, attendance at pram-walking groups and consultations will be logged and participants’ use of strategies from the consultations (intervention group only) will be assessed at three and six months. Approximately 20% of the consultations will be recorded and reviewed by another researcher to assess consistency and fidelity of the intervention delivery. Additionally, qualitative in-depth interviews will be used to assess the acceptability of the intervention to the target group and assess possible control contamination. A researcher who is not involved in the main trial will conduct interviews and participants will be made aware that their comments will be anonymized to avoid the primary research team identifying them.

#### Blinding

Blinding of the CI and participants is carried out at baseline since outcomes are taken prior to group allocation. At three- and six-month follow-ups, steps have been taken to minimize potential bias from a lack of blinding of the CI. This includes using objective measures to assess physical activity, fitness weight and body composition according to standardized protocols. Other secondary outcomes are assessed through self-administered questionnaires.

#### Data analysis

Actilife 5 will be used to analyze accelerometer data in the following ways: ‘raw’ accelerometry output (that is, counts per minute (cpm) averaged over the measurement period), time (minutes) spent in moderate to vigorous intensity physical activity per week, continuous bouts of at least 10 minutes of moderate-vigorous physical activity (MVPA) and, percentage of time spent in MVPA. The calculation of MVPA is based on accepted cut-points for adult women in free-living conditions [65-67]. However, there is wide variation in the ability of cut-point equations to accurately assess physical activity in different intensity zones. Cpm is, therefore, an important measure as it provides an estimate of change in total physical activity and has been validated in free-living conditions against criterion methods, such as energy expenditure [68].

Trial data will be analyzed according to intention-to-treat principles with all participants included according to initial group allocation. To minimize the number of statistical tests conducted, Analysis of Covariance (ANCOVA) will be used with a repeated measures design and group allocation as a between groups factor. Covariates, which have been shown to influence physical activity participation, will be included (for example, participant’s age, participant’s BMI and physical activity stage of change). Population-specific covariates (for example, infant’s age and number of children, and so on) will also be added to the model. Bonferroni *post-hoc* testing will be used to investigate intervention efficacy (between-groups change to three months) and assess maintenance effects (whether change is sustained to six-month follow-up). Statistical analysis will be conducted on all secondary outcomes, also using this approach.To assess whether change in the main outcome (physical activity participation) occurred as a result of change in the psychological mediators, mediation analysis will be conducted using the Sobel test, which involves testing the null hypothesis that there is no difference between the total and direct effects, that is, the assumption that there are no indirect effects of the psychological mediators on physical activity behavior change [69]. This approach provides greater statistical power than the more traditional Baron and Kenney [70] approach. Given the small sample size present in the current study, this is an important consideration and should ensure Type II error is minimized.

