## Methods/design

### Study design

The MAMMiS study is a single-site randomized, controlled trial (RCT) investigating the efficacy of a motivational and behavioral intervention consisting of two physical activity consultations and a 10-week group pram-walking program on physical activity behavior change. Participants are recruited over a one-year period from a National Health Service (NHS) region within Central Scotland through a variety of strategies (described below). Following eligibility screening, participants give informed consent and complete baseline outcome assessments. These assessments are repeated at three and six months follow-up (Figure 1). The primary outcome is weekly participation in physical activity measured *via* accelerometers. The trial is conducted and reported according to Consolidated Standards of Reporting Trials (CONSORT) guidelines [29] and includes psychological mediators to identify whether change in physical activity occurs through changes to the hypothesized determinants. Acceptability of the intervention is evaluated in a separate study through interviews with participants.

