### Sample size

Based on calculations carried out by an independent statistician, 31 participants per group are required in order to detect an effect of 63.83 minutes/week of moderate-vigorous physical activity participation. This assumes power of 90%, 5% significance level with a two-sided unpaired *t*-test to detect change from pre- to post-test between the intervention and control group using a pooled standard deviation of 75 minutes/week. This sample size calculation is based on data from a previous study comparing a 12-week physical activity intervention in insufficiently active breast cancer survivors with usual care [35]. Comparable to the present study, the main outcome in that study was change in weekly minutes of moderate-vigorous intensity physical activity from baseline to three months measured using accelerometers [35]. This study was used as no previous reports of postnatal physical activity promotion interventions had used accelerometers to measure change in physical activity behavior. An increase of 60 minutes of moderate-vigorous physical activity (for example, brisk walking) per week is clinically significant for cardiovascular health [36]. Assuming a 20% dropout (in line with similar studies [14,17]) up to 76 postnatal women will be sought.

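### The repeated-measures ANCOVA named for the primary analysis, as conventionally fitted, does not by itself give the intention-to-treat analysis of all participants that the plan promises

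*Protocol article*

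**What the plan says.** The Data analysis section sets the population: "Trial data will be analyzed according to intention-to-treat principles with all participants included according to initial group allocation". The next sentence sets the model: "Analysis of Covariance (ANCOVA) will be used with a repeated measures design and group allocation as a between groups factor". Both time points are then tested from that one model: "Bonferroni *post-hoc* testing will be used to investigate intervention efficacy (between-groups change to three months) and assess maintenance effects". The same approach is to be used for all secondary outcomes.

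The visits are baseline, three and six months; of the baseline assessments, Study design says "These assessments are repeated at three and six months follow-up". The Aim section places the main hypothesis at three months and lists six-month efficacy as a secondary aim.

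Missing outcomes are expected. Sample size says "Assuming a 20% dropout (in line with similar studies [14,17]) up to 76 postnatal women will be sought". Physical activity sets a validity rule, "Participants with at least four valid days of data monitoring will be considered as having a valid dataset", and softens it: "A second measurement week is used if wear time criteria has not been met during the first measurement week".

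The article names no imputation method and no mixed or likelihood-based model. It also does not say that women with incomplete data are excluded.

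**The concern.** The article fixes both a population and a model, and the model in its usual form does not produce that population. The conventional repeated-measures ANCOVA needs a complete row per woman. Under that fit, attendance and monitor wear at six months decide who counts in the primary three-month comparison, although the main question has been answered by then.

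Two things are at stake. Valid three-month data may be thrown away. Also, the women who remain may differ between arms. Participants know their allocation, and the investigator who delivers the consultations also carries out the follow-up assessments unblinded (Intervention, Outcomes and Blinding sections). If intervention women whose activity changed little are more likely to miss the six-month visit, the three-month contrast among completers is too favourable, while the report calls it intention-to-treat.

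**Working it through.** **Inputs from the Sample size section:** difference 63.83 min/week, SD 75, two-sided 5%, 90% power, unpaired t-test on change, 31 per group, 20% dropout, up to 76 women. **Assumptions, not in the document:** when the dropout occurs, how many retained women lack a valid accelerometer dataset, and equal loss in the two arms.

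**1. The plan's own figure.** The plan states that "31 participants per group are required in order to detect an effect of 63.83 minutes/week of moderate-vigorous physical activity participation". The noncentrality is 63.83 / (75 × √(2/31)) = 63.83 / 19.05 = 3.35. Noncentral-t power is 0.909 at 31 per group and 0.900 at 30, so the stated size reproduces. For dropout, 62 / 0.80 = 77.5, so 78. The stated 76 equals 2 × 38, from 31 × 1.2 = 37.2 rounded up. The two totals differ by two women, which does not matter here.

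**2. Women kept at the stated dropout.** 76 × 0.80 = 60.8, about 61 kept and about 15 left out. Power at 30 per group is 0.900, the design target.

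**3. If some retained women also lack a valid dataset at some visit.**

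| Further loss (assumed) | Women kept | Power |
|---|---|---|
| 0% | 60.8 | 0.90 |
| 5% | 57.8 | 0.88 |
| 10% | 54.7 | 0.87 |
| 15% | 51.7 | 0.84 |

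Power is computed at half the total per group, rounded down (30, 28, 27 and 25).

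**4. Three-month data discarded.** The plan does not say how the 20% divides between the time before and the time after three months. With 60.8 women complete, the standard error under complete-case fitting is larger by √(n at three months / 60.8).

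| Valid at three months (assumed) | Three-month values discarded | SE ratio | Power, all three-month data | Power, completers |
|---|---|---|---|---|
| 80% (60.8) | 0 | 1.00 | 0.90 | 0.90 |
| 90% (68.4) | 7.6 | √(68.4/60.8) = 1.06 | 0.93 | 0.90 |
| 100% (76) | 15.2 | √(76/60.8) = 1.12 | 0.96 | 0.90 |

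So between none and about 15 valid three-month values are lost, and power falls by at most about 6 points from what the collected data could give.

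**5. Selection bias, as an illustration only.** A simulation used 38 women per arm, a true three-month effect of 63.8 and SD 75, with 10% missing at three months at random. Of the rest, control women missed six months with probability 10%. Intervention women missed it with a probability that rose steeply as their three-month change fell below about −15 min/week. On average 77% had all visits. The mean estimated effect was 63.8 from all women with three-month data and 84.7 from women with every visit. The mechanism is strong and assumed. The result shows that the exposure exists and in which direction it could run, not how large it would be in this trial.

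**The case against.** The strongest reply is that deletion is nowhere stated. The article says that all participants are included and names neither a procedure nor an estimation method. Imputation before the ANCOVA, or a likelihood fit of a repeated-measures model with covariates, would be compatible with its wording. Missing-data detail is commonly left to a full protocol or analysis plan. This stands in part. A reader might infer that the method cannot deliver intention-to-treat, and the document does not support that. Silence on missing data alone would be no finding. The point survives because the article fixes a model whose usual fit contradicts the population fixed one sentence before it.

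Three further points stand. The second measurement week will recover some invalid datasets. Dropouts at each stage will be reported in line with CONSORT (Process measures), so attrition would be visible. The article gives a reason for one joint model, namely to limit the number of tests; a mixed model over both follow-up visits keeps that advantage.

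Two stronger readings are tempting and fail. One is that the trial becomes underpowered: at the planned 20% loss it does not, and lower figures need further loss that the document does not predict. The other is that the effect would be overstated by 25%. That comes from supposing that 20% of the intervention arm leave with no gain: 0.8 × 63.83 = 51.1, and 63.83 / 51.1 = 1.25. It concerns women with no follow-up value, whom a mixed model's primary estimate also leaves out. It therefore does not measure the difference between the two methods.

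**Conclusion.** The point holds in a conditional form. With no missing-data approach stated, the named model in its conventional fit would analyse only women with valid data at every visit, about 61 of 76 at the plan's own dropout. This conflicts with the promise that all are included. Power remains near 90%. The cost is the loss of between none and about 15 valid three-month values, a selection bias whose size cannot be derived from the document, and a label that would not describe the analysis.

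The conclusion rests on the conventional fit being used and on some women being lost after three months. If all losses occur before three months, no three-month values are discarded, but the label is still inaccurate.

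**What to change.** Replace the repeated-measures ANCOVA with a likelihood-based linear mixed model: three- and six-month MVPA as outcomes, group by visit, baseline MVPA and the planned covariates, unstructured covariance, REML. Include every randomized woman with at least one valid follow-up value, in her allocated group. Take the three-month contrast as primary and the six-month contrast as secondary from this model, and use the same form for the secondary outcomes.

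Add a sensitivity analysis covering all randomized women, in which intervention women with missing outcomes are given no gain over baseline. The 51.1 min/week figure can serve there as an assumed illustration and nowhere else. Describe the primary set as all randomized women with available outcome data.

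The change costs some wording and a different fitting procedure, with no extra data or visits. The article describes the trial as active, with 65 women enrolled at submission, so the change could be fixed before analysis. The downside is that the primary model assumes data are missing at random. It does not recover women with no follow-up value; only the sensitivity analysis addresses them.

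### The efficacy contrast, as most naturally read, is a change from baseline and not a baseline-adjusted comparison; it is valid, but gives up precision that the trial has already collected

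*Protocol article*

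**What the plan says.** The Data analysis section of the protocol article names ANCOVA with a repeated-measures design and group as the between-subjects factor. Post-hoc tests address efficacy, defined as "between-groups change to three months", and then whether that change lasts to six months. On adjustment it says "Covariates, which have been shown to influence physical activity participation, will be included". The examples given are age, BMI, stage of change, infant's age and number of children. Both lists are illustrative and open-ended. All secondary outcomes are to be analysed in the same way.

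Under Study design, outcomes are taken at baseline and "These assessments are repeated at three and six months follow-up". The Blinding section confirms that baseline outcomes are measured before allocation.

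The Sample size section uses the same scale as the efficacy contrast. It plans an unpaired t-test "to detect change from pre- to post-test between the intervention and control group using a pooled standard deviation of 75 minutes/week", and says of the source study that "the main outcome in that study was change in weekly minutes of moderate-vigorous intensity physical activity from baseline to three months measured using accelerometers".

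**The concern.** If efficacy is a between-group difference in change within a repeated-measures model, baseline MVPA is part of the outcome. Subtracting the baseline fixes its slope at 1, whereas a covariate lets the data estimate the slope. When the best slope is below 1, subtraction over-corrects. The estimate then carries avoidable variance, and in any single trial it leans towards the arm that happens to start lower.

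The trial is small, with about 62 completers intended, and baseline MVPA is likely to be the strongest available predictor of later MVPA. Stage of change, which is a named covariate, is a weak stand-in because eligibility admits only the contemplation and preparation stages. The Data analysis section itself cites the small sample when it chooses its mediation method for power, and the same reasoning applies to the primary comparison. At stake is the width of the primary interval and of every secondary interval built the same way.

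**Working it through.** **Inputs from the Sample size section.** The stated requirement is "31 participants per group are required in order to detect an effect of 63.83 minutes/week of moderate-vigorous physical activity participation". The test is a two-sided, unpaired t-test at the 5% level, and the target power is 90%. The SD is 75 min/week, read as the SD of the change. Dropout is 20%, and "up to 76 postnatal women will be sought".

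**Assumption.** The baseline-to-three-month correlation r is not given, so it is shown over 0.3 to 0.9.

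**Step 1: reproduce the plan's figure.** For a two-sided 5% t-test with difference 63.83 and SD 75, the noncentral t gives power 0.8999 at 30 per group and 0.909 at 31. The smallest n that reaches 90% is 31, as stated.

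**Step 2: compare the two analyses, equal SD s at both visits.**
- Change score: variance 2s²(1 − r).
- Baseline-adjusted: residual variance s²(1 − r²).
- Ratio: (1 − r²) / [2(1 − r)] = (1 + r)/2, which is below 1 for every r < 1.
- With the change SD fixed at 75, the adjusted SD is 75 × √((1 + r)/2).

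Power is at 31 per group, with one further degree of freedom spent on baseline.

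| r | Variance ratio | Adjusted SD | Power |
|---|---|---|---|
| Change score | 1 | 75 | 90.9% |
| 0.3 | 0.65 | 60.5 | 98.3% |
| 0.5 | 0.75 | 65.0 | 96.8% |
| 0.7 | 0.85 | 69.1 | 94.7% |
| 0.9 | 0.95 | 73.1 | 92.2% |

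A simulation of 20,000 trials per value of r, at 31 per group, gave variance ratios of 0.657, 0.755, 0.865 and 0.975. These are slightly above the formula because the slope has to be estimated.

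**Step 3: relax the equal-SD assumption.** Let k be the follow-up SD divided by the baseline SD. The ratio becomes k²(1 − r²) / (1 + k² − 2rk), so the proportional reduction is (1 − rk)² / (1 + k² − 2rk). With k = 1.25, an assumption made for illustration:
- r = 0.3: 0.3906 / 1.8125 = 22%
- r = 0.5: 0.1406 / 1.3125 = 11%
- r = 0.7: 0.0156 / 0.8125 = 2%
- r = 0.9: 0.0156 / 0.3125 = 5%, the same as with equal SDs

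The reduction is zero where rk = 1, for example r = 0.7 with k = 1.43, because the best slope is then exactly 1. Apart from the small cost of estimating the slope, it is never negative. A follow-up SD below the baseline SD makes it larger.

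**Step 4: sensitivity to chance imbalance, equal SDs.** Given a baseline difference D between arms, the change-score estimate is displaced by (1 − r)D in favour of the arm that starts lower. A change SD of 75 implies a raw SD of 75/√(2(1 − r)): 63.4, 75.0 or 96.8 at r = 0.3, 0.5 or 0.7. At 31 per group, one standard error of D is that SD × √(2/31): 16.1, 19.1 or 24.6 min/week. The displacement is then 0.7 × 16.1 = 11.3, 0.5 × 19.1 = 9.5 or 0.3 × 24.6 = 7.4 min/week, which is 12% to 18% of 63.83.

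**The case against.** **The role of baseline is inferred.** The article does not say which visits form the repeated factor. The name ANCOVA would also fit three- and six-month values adjusted for baseline, and the open covariate lists could take in prior activity. This stands as a limit on certainty. The definition of efficacy as change, and a sample size built on change, still make the group-by-time reading the more natural one.

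**The detail may sit in an analysis plan not shown.** That would answer a complaint about an incomplete covariate list. It does not answer this point, because the article itself fixes the efficacy contrast as change.

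**The planned analysis is sound and adequately powered.** This stands. A reader might infer from Step 4 that the planned estimate is biased. It is not: over repeated randomizations the change contrast is unbiased, and the displacement is conditional on the imbalance that happens to occur. A reader might also infer that the trial is underpowered or its sample size wrong. The stated 31 per group reproduces, and it matches the contrast.

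**The gain may be smaller than the headline figures.** This also stands. It depends on an unstated r and on the SD ratio, and recruiting only insufficiently active women may compress the baseline spread relative to follow-up. The comparator in the table is an unadjusted t-test on change, whereas the planned model carries covariates that may recover some precision.

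**A repeated-measures model that includes baseline is not inherently inefficient.** Correct: a longitudinal model that constrains the arms to a common baseline mean recovers the precision. Removing baseline from the outcome is therefore one acceptable route, not a requirement.

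**Conclusion.** The point holds as a matter of efficiency and clarity, not of validity. As most naturally read, the plan compares change from baseline and does not name baseline MVPA as a covariate. With equal SDs, adjusting for baseline would cut the variance by 35%, 25%, 15% or 5% at r = 0.3, 0.5, 0.7 or 0.9. With a follow-up SD 1.25 times the baseline SD, the first three fall to about 22%, 11% and 2%. The direction is general, but the size is uncertain because the article gives neither r nor the visit-specific SDs. The powers above are at the two-sided 5% level of the Sample size section; any Bonferroni division of that level is a separate matter.

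The change is worth making because the plan has little slack. Taking 20% dropout from 76 leaves 60.8 women, about 30 per group, where the change-score t-test sits at 89.99%.

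**What to change.** State in the Data analysis section that the primary estimate is the between-group difference in three-month weekly MVPA, adjusted for baseline weekly MVPA. Either of two models will do:
- the three- and six-month values as outcomes, with baseline MVPA as a covariate; or
- a longitudinal model of all three visits with a common baseline mean across arms.

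Apply the same rule to each secondary outcome, using its own baseline value. Keep the t-test on change as the sample size basis, since it is generally conservative for the adjusted analysis. If baseline adjustment was already intended, the same sentence makes that explicit.

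The cost is one sentence and about one degree of freedom per model. No new data are needed, because baseline outcomes are collected before allocation.
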